### 4.1. Interventions

Patients included in the study will be randomized to receive the following:

#### 4.1.1. Exercise and Neuromodulation Protocol

Participants allocated to the intervention group will participate in a structured, progressive program focusing on core stabilization and spinal motor control [28]. The intervention will be delivered through supervised sessions, each lasting 60 min, consisting of two consecutive components: 30 min of tDCS followed by 30 min of targeted exercise therapy. Sessions will be organized into progressive phases tailored to the individual’s capabilities and clinical progression. The duration of each rehabilitation phase will be determined by the patient’s level of disability and the pain intensity. Advancement to subsequent phases will occur when functional capacity and symptom control are sufficient to safely achieve the objectives of the next stage. We will implement an exercise protocol that has been previously published for patients with the same diagnosis (Table 2) [29]. Table 2 provides a comprehensive overview of all stages of the structured motor control rehabilitation protocol for PSPS-T2, encompassing the specific objectives and exercise parameters.

#### 4.1.2. Neuromodulation Protocol

The transcranial direct current stimulation protocol will consist of 24 sessions administered twice per week over a 12-week period. During each session, a constant direct current will be applied for 30 min at an intensity of 1 mA [30,31]. The stimulation will target the left DLPFC using two saline-soaked sponge electrodes (35 cm^2^) (Ionclinics & Deionic S.L., based in L’Alcúdia (Valencia), Spain). Electrode placement will follow the International 10–20 electroencephalography (EEG) system [32]. The anodal electrode will be positioned over site F3 (left DLPFC), and the reference (cathodal) electrode will be placed over the left supraorbital area [26]. To ensure participant safety and minimize discomfort, each session will include a 30-s ramp-up and ramp-down period at the beginning and end of stimulation [33,34].

#### 4.1.3. Exercise and Sham Neuromodulation Protocol

Participants assigned to the placebo group will be subjected to a sham tDCS protocol designed to simulate the procedures of the active intervention without delivering sustained cortical stimulation. The sham protocol will also comprise 24 sessions, conducted twice weekly over a 12-week period, thereby aligning with the timeline and structure of the experimental group. Electrode placement will mirror that of the active stimulation condition, with the anodal electrode positioned over site F3 (left dorsolateral prefrontal cortex) and the reference electrode placed over the left supraorbital area, using 35 cm^2^ saline-soaked sponge electrodes. During each session, the tDCS device (Valencia, Spain) will administer a brief 30-s ramp-up of current to replicate the initial scalp sensations associated with active stimulation, followed by an immediate ramp-down, after which no current will be delivered for the remainder of the session. A second 30-s ramp-down will be programmed at the conclusion of the 30 min period to further maintain the illusion of continuous stimulation [34]. This sham procedure has been validated in previous studies to effectively blind participants by reproducing the typical transient sensory experiences of tDCS without inducing significant neuromodulatory effects [26].

## 5. Patient-Reported Outcome Measures

### 5.1. Baseline Characteristics

A comprehensive series of evaluations and analyses of body dimensions and proportions will be conducted. Data will be systematically collected on variables including age, sex, weight, height, occupation, and date of initial diagnosis. Furthermore, general health status will be documented to identify potential comorbidities, along with the educational level of each participant. Additionally, the duration of medication use will be recorded, with medications classified into the following categories: non-opioid analgesics, strong opioids, weak opioids, and adjuvant drugs. The primary and secondary outcome variables are detailed below, with data for each variable systematically collected at all scheduled assessment time points.

### 5.2. Primary Outcome

#### Disability

The ODI is the most widely used and validated instrument for assessing functional impairment resulting from low back pain [35]. This self-administered questionnaire encompasses ten domains that evaluate limitations in activities of daily living [36]. Each domain is scored on a scale of 0–5, with higher scores indicating greater disability. The total ODI score is derived by summing the individual domain scores, dividing by the maximum possible score, and expressing the result as a percentage (e.g., a summed score of 25 out of 50 yields 50%) [37]. The Spanish version of the ODI has undergone psychometric validation, demonstrating high sensitivity and specificity in assessing the functional status of individuals with low back pain [38]. Psychometric evaluations revealed that the ODI exhibited strong construct validity and satisfactory internal consistency. Furthermore, the ODI has demonstrated high test–retest reliability, with correlation coefficients ranging from 0.73 to 0.99, depending on the interval between assessments [39].

### 5.3. Secondary Outcomes

#### 5.3.1. Fear of Movement

Kinesiophobia is defined as an “excessive, irrational, and debilitating fear of physical movement and activity, resulting from a feeling of vulnerability due to a painful injury or the risk of reinjury” [40]. The most widely used instrument to assess kinesiophobia is the Tampa Scale for Kinesiophobia (TSK), which has been specifically employed to measure fear of movement in individuals with low back pain [41]. This scale addresses fear-avoidance beliefs, work-related injuries, repetitive strain injuries, and fear of reinjury. The TSK consists of 11 items that distinguish between positive and negative statements related to movement and pain beliefs [42]. Responses are rated on a 4-point Likert scale, ranging from 1 (“strongly disagree”) to 4 (“strongly agree”). The total score ranges from 11 to 44, with higher scores indicating greater Kinesiophobia [43]. The internal consistency of the TSK in populations with low back pain has been reported to range from Cronbach’s α = 0.70 to 0.83, while test–retest reliability values vary between r = 0.33 and 0.59 [44].

#### 5.3.2. Self-Efficacy

Perceived self-efficacy in the context of chronic pain refers to an individual’s confidence in their ability to cope with symptoms, maintain physical function, and manage pain. To assess this construct, the Chronic Pain Self-Efficacy Questionnaire developed by Martín-Aragón et al. (1998) will be utilized, which has been validated in Spanish-speaking populations [45]. This version demonstrated psychometric properties comparable to those of the original scale, exhibiting high internal consistency (α = 0.87). The questionnaire consists of 19 items arranged on a Likert-type scale ranging from 0 to 10, where 0 indicates feeling completely incapable, 5 indicates feeling moderately capable, and 10 indicates feeling fully capable [46].

#### 5.3.3. Pain-Related Catastrophizing Thinking

The Pain Catastrophizing Scale (PCS) will be used to assess pain-related catastrophizing among the study participants. The PCS is a self-administered validated questionnaire consisting of 13 items grouped into three subscales: rumination, magnification, and helplessness [47]. Each item is scored on a 4-point Likert scale ranging from 1 (“not at all”) to 4 (“all the time”), resulting in a total score ranging from 13 to 52. Higher scores indicate greater pain catastrophizing [48]. The Spanish version of the PCS will be administered, which has been validated and shows satisfactory psychometric properties, including an internal consistency (Cronbach’s alpha) of 0.79 and a test–retest reliability of 0.84 [49].

#### 5.3.4. Quality of Life

The Short Form-12 Health Survey (SF-12) is a widely used and validated instrument for assessing health-related quality of life across physical and mental domains. It is a shorter alternative to the Short Form-36 Health Survey (SF-36) and was developed to reduce the respondent burden while maintaining robust psychometric properties [50]. The SF-12 yields two composite scores: the Physical Component Summary and the Mental Component Summary, derived from 12 questions representing eight health domains: physical functioning, role limitations due to physical and emotional problems, bodily pain, general health, vitality, social functioning, and mental health [51]. The SF-12 has demonstrated strong internal consistency and validity in both general and clinical populations and is sensitive to changes in health status. It has been validated in multiple languages, including Spanish, and has shown high concordance with SF-36 component scores. This makes it a practical tool for large-scale epidemiological studies, clinical trials, and routine health assessments [50].

#### 5.3.5. Central Sensitization (CS)

The Central Sensitization Inventory (CSI) is a validated self-report questionnaire developed to identify symptoms associated with CS and related disorders. CS refers to the amplification of neural signalling within the central nervous system, which elicits pain hypersensitivity, often independent of peripheral nociceptive inputs [52]. The CSI is composed of two parts: Part A, which contains 25 items assessing the frequency of health-related symptoms associated with CS (e.g., unrefreshing sleep, fatigue, and concentration difficulties), and Part B, which enquires about previously diagnosed central sensitivity syndromes such as fibromyalgia, irritable bowel syndrome, and migraine [53]. Each item in Part A is scored on a 5-point Likert scale ranging from 0 (“never”) to 4 (“always”), resulting in a total score between 0 and 100. A score of ≥40 indicates clinically relevant central sensitization [54]. The CSI has demonstrated strong psychometric properties, including excellent internal consistency (Cronbach’s α = 0.88) and test–retest reliability [55]. The CSI is increasingly used in both clinical and research settings to characterize pain mechanisms in patients with chronic pain conditions, including low back pain, temporomandibular disorders, and chronic fatigue syndrome, supporting its utility in multidimensional pain assessment frameworks [52].

#### 5.3.6. Pain Perception

The VAS is considered the most representative tool for pain perception assessment and is the preferred option because of its simplicity and ease of use. The version employed in this study used a 0–10 numerical rating scale. This scale is an effective instrument for the subjective and sensitive quantification of pain intensity within this range. A score of 0 represents the complete absence of pain as perceived by the individual, while a score of 10 indicates the worst pain imaginable [56]. The VAS has demonstrated a superior discriminative capacity compared with descriptive or fixed-point scales. Furthermore, the VAS has shown excellent reliability, with a Cronbach’s alpha of 0.97 (95% CI: 0.96 to 0.98) [57].

#### 5.3.7. Neuropathic Pain

DN4 is considered one of the most sensitive tools for diagnosing neuropathic pain, demonstrating a high capacity to discriminate between neuropathic and nociceptive pain. The DN4 has been validated in patients with LBP resulting from disc herniation, spinal stenosis, degenerative disc disease, spinal pain, lumbar spine degeneration, spinal surgery, and scoliosis. A cut-off score of 4 on the DN4 has shown a sensitivity of 80% and a specificity of 92% for the diagnosis of neuropathic pain in individuals with LBP [58]. Each participant was asked to describe their pain based on the first seven descriptors of neuropathic pain included in the DN4 questionnaire to calculate the DN4 interview sub-score (0–7). The intraclass correlation coefficient for the DN4 was 0.86 (95% CI: 0.80–0.91), indicating good test–retest reliability [59].

#### 5.3.8. Depressive Symptoms

The Beck Depression Inventory-II (BDI-II) is a 21-item self-report questionnaire designed to assess the severity of depressive symptoms in adults and adolescents aged ≥ 13 years [60]. This revised version of the inventory was developed to evaluate symptoms consistent with the diagnostic criteria for depressive disorders, as outlined in the Diagnostic and Statistical Manual of Mental Disorders, Fourth Edition (DSM-IV; American Psychiatric Association, 1994) [61]. The test–retest reliability of the BDI-II in chronic pain populations has been assessed in multiple studies, which have generally demonstrated high temporal stability. For instance, in patients with chronic pain, the test–retest correlation coefficient of the BDI-II typically ranges from 0.80 to 0.90, indicating good-to-excellent reliability over time [62].

## 6. Program Feasibility and Safety: Attendance and Compliance with Protocol

Adherence to rehabilitation protocols in patients diagnosed with PSPS-T2, formerly designated as Failed Back Surgery Syndrome, is influenced by multiple determinants. Social and environmental factors that bolster adherence to and compliance with home-based exercise regimens are critical in this population [63]. Moreover, adherence is affected by therapist support, the characteristics of the rehabilitation environment, and the progression rate of the exercise program, as demonstrated in chronic lower back pain studies [64]. Rehabilitation adherence will be operationalized as the proportion of patients who complete all scheduled assessments, in accordance with validated approaches in chronic pain rehabilitation research [65]. Early-stage individualized training will be implemented to promote protocol adherence and mitigate the risk of adverse events, particularly given the PSPS-T2 complexity and postsurgical challenges [66].

## 7. Oversight and Monitoring

Specific protocols will be implemented to ensure data integrity and participant well-being. The principal investigators will collaborate with physicians to monitor and evaluate the study’s progress and safety measures. The study analysis will incorporate data collected before the intervention’s conclusion. An Independent Safety Monitor, who also serves as the secretary of the approving ethics committee, will receive and review biannual progress reports. These reports include information on participant recruitment, retention and attrition rates, and adverse events. Upon completion of the study, a comprehensive final report will be prepared summarizing adverse events and including participants’ explanations for withdrawal. The reasons for withdrawal will be examined and compared with the researchers’ initial expectations to identify the patterns and potential contributing factors. Additionally, an evaluation will be conducted to predict participants at risk of early withdrawal to develop strategies to minimize attrition and enhance the reliability of study outcomes. The Data Safety Monitoring Plan stipulates that any serious adverse event must be reported to the Ethics Committee within 48 h. If an unexpected serious adverse event is deemed to present an increased risk to participants, the study will be suspended if the Independent Safety Monitor determines this to be necessary based on the frequency or severity of the events.

## 8. Data Collection and Analysis

### 8.1. Data Collection

The data collection strategy has been meticulously designed to uphold the rigorous standards of data quality, integrity, and confidentiality throughout the randomized clinical trial. Upon acquisition of paper-based records, the study coordinator will oversee all data management processes. Encrypted Excel databases with double-entry verification will be used to ensure participant confidentiality and enhance data accuracy. Methodological parameters, including sample size, eligibility criteria, randomization and blinding procedures, treatment protocols, and outcome variables, are predefined and are comprehensively detailed in the methodology section. Data will be collected through uniform documents and digital platforms, with any unfinished submissions consistently removed to ensure uniformity and reliability.

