### 2.4. Procedure

Upon formation of the groups, four distinct sample collections will be undertaken at the following intervals: Pre, Post-1 month, Post-3 months, and Post-6 months (Figure 1). At each designated measurement point, a comprehensive follow-up of the studied variables will be meticulously conducted and recorded in the “Data Collection Notebook”. This document is specifically crafted to capture both primary and secondary variables, thereby ensuring a systematic approach to data collection throughout the study. The research comprises two groups, each structured to meet the previously outlined objectives: the E_tDCS_ and E_SHAM_ groups. All assessments will be performed bilaterally to enable within-subject comparisons.

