## 4. Sample Size

The sample size will be determined using G*Power software (Franz Faul, University of Kiel, Kiel, Germany; version 3.1.9.2). Statistical analysis will be conducted using repeated measures analysis of variance (ANOVA). The calculation will be based on the primary outcome variable, the Oswestry Disability Index (ODI), with the assumption of a Cohen’s effect size of 0.81 [26], a statistical power of 0.95, an alpha error of 0.05, and two study groups. The estimated total sample size is 30. To accommodate a potential dropout rate of 40% during follow-up, the minimum required number of participants has been adjusted to 42 (experimental group = 21; control group = 21). This rate is consistent with previous evidence: a review of clinical studies on chronic pain reported that dropout can vary widely, ranging from 5% to 60% depending on the study, type of pain, duration, and intervention. The selected effect size is categorized within a large range (0.60–1.19), as corroborated by previous studies [27].

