#### 8.2.2. Analysis of the Outcome Measures

In alignment with the CONSORT (Consolidated Standards of Reporting Trials) guidelines for randomized controlled trials, a per-protocol analysis will be undertaken. The Shapiro–Wilk test, along with visual inspection of boxplots and histograms, will be employed to evaluate the assumption of normality, while Levene’s test will be used to assess the homogeneity of variances. Descriptive statistics, including mean ± SD, frequencies, and percentages, will be used to summarize the baseline characteristics of the participants. To investigate the acute and follow-up effects of E_tDCS_ and E_SHAM_, a 2 × 5 repeated measures ANOVA (two groups × five time points: baseline, post-intervention, 1-month, 3-month, and 6-month follow-ups) will be conducted. Main effects (time and group) and interaction effects (group × time) will be analyzed using SPSS version 28 (IBM Corp., Armonk, NY, USA) and JASP (Version 0.15.0.0.0; JASP Team, Amsterdam, The Netherlands, 2023). In instances where significant interactions are identified, pairwise post hoc comparisons with Bonferroni correction will be conducted. Cohen’s d and 95% confidence intervals (CIs) will be used to report effect sizes and the magnitude of observed changes. If the data violate parametric assumptions, non-parametric alternatives (for example, Mann–Whitney test) will be applied. In the event of participant attrition or a decrease in statistical power below the predefined 80% threshold, an intention-to-treat analysis will be conducted to ensure the robustness of the findings [67]. All statistical analyses will be performed using JASP software (version 0.18.3.0; JASP Team, Amsterdam, The Netherlands) by an independent statistician who is blinded to group allocation and uninvolved in data collection.

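### Unfinished submissions are to be removed without limit, and under a repeated measures ANOVA one removed ODI form also drops that participant's other visits from the primary test

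*Protocol article*

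**What the plan says.** Section 8.1 (Data Collection) describes collection on standard forms and digital platforms, "with any unfinished submissions consistently removed to ensure uniformity and reliability". It does not say what counts as a submission or as unfinished, and it makes no exception.

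Section 4 names the ODI as the primary outcome. Section 5.2 describes it as ten self-completed domains, with the total "derived by summing the individual domain scores, dividing by the maximum possible score, and expressing the result as a percentage". The only worked example there is a form scored out of 50. Nothing is said about a blank domain.

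Section 8.2.2 gives the main analysis as a "repeated measures ANOVA (two groups × five time points: baseline, post-intervention, 1-month, 3-month, and 6-month follow-ups". It also states that "a per-protocol analysis will be undertaken", and adds: "In the event of participant attrition or a decrease in statistical power below the predefined 80% threshold, an intention-to-treat analysis will be conducted". No method for missing values accompanies that sentence.

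Section 2.4 gives a different number of assessments: "four distinct sample collections will be undertaken at the following intervals: Pre, Post-1 month, Post-3 months, and Post-6 months". Both counts are used below.

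**The concern.** The rule and the model work together. The rule turns a partly answered form into no form. A classical repeated measures ANOVA then turns one absent visit into an absent participant, because each person must have a value at every level of the time factor. The article does not use the words complete-case or listwise, but that is how the named method behaves. One unfinished ODI form could therefore cost the answers on that form and also the participant's finished ODI forms from the other visits.

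Two things are at stake. Precision falls in a trial of only 42 people. The people analysed are also those able and willing to finish every form. In patients who enter with pain of at least 7 out of 10 and answer nine instruments at each assessment (Table 1), finishing forms is plausibly related to pain and disability. If that relation differs by arm, the primary comparison can be biased.

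How much is lost depends on what a submission is. If it means the whole visit set, a gap in any of the other eight questionnaires could remove a finished ODI. If it means only an abandoned entry, little is lost.

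**Working it through.** **Inputs from the article**
- 30 participants required, 40% dropout allowance, 42 randomised (Section 4).
- Five time points (Section 8.2.2) or four (Section 2.4).

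**Input assumed, because the documents give none**
- q, the chance that an ODI form is unfinished at a given visit: 5%, range 2% to 10%.

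**Step 1. The plan's own figure.** 30 × (1 + 0.40) = 42, which reproduces the stated number. With 40% dropout, 42 × 0.60 = 25.2, so about 25 people complete follow-up. That is already below 30 before any form is removed. This is a separate matter and is used here only as the starting number.

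**Step 2. People with every ODI form, omissions independent across visits.** P(all v forms finished) = (1 − q)^v.

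| q | v = 5 | of 25 | v = 4 | of 25 |
|---|---|---|---|---|
| 2% | 0.98^5 = 0.904 | 22.6 | 0.98^4 = 0.922 | 23.1 |
| 5% | 0.95^5 = 0.774 | 19.3 | 0.95^4 = 0.815 | 20.4 |
| 10% | 0.90^5 = 0.590 | 14.8 | 0.90^4 = 0.656 | 16.4 |

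With no dropout at all, five visits would leave 38.0, 32.5 and 24.8 of 42.

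**Step 3. Omissions clustered within people.** Independence overstates the loss if the same people tend to leave forms unfinished. With a beta-binomial model (mean 5%, five visits, intra-person correlation r), put a + b = 1/r − 1 and b = 0.95(a + b). Then P(all finished) is the product over i = 0 to 4 of (b + i)/(a + b + i).
- r = 0.2: a + b = 4, b = 3.8; 0.950 × 0.960 × 0.967 × 0.971 × 0.975 = 0.84 (rounded up from 0.835).
- r = 0.4: 0.87.
- r = 0.6: 0.90.

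So 84% to 90% would have all five forms, or about 21 to 23 of 25, against 19 under independence.

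**Step 4. Does the fallback repair this?** The intention-to-treat analysis is triggered by attrition or by low power, not by an unfinished form. With a 40% dropout allowance it would very probably be triggered. Even so, a form that has been removed leaves no value to analyse, and no method for absent values is named.

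**The case against.** The strongest objection concerns the reading of the rule. Submission is undefined, and the sentence may be aimed at abandoned entries rather than an ODI with one blank domain. That stands: a reader might infer that a single omitted item certainly removes a participant, and the article does not say so. What can be criticised is a rule with no definition and no limit, which permits that reading.

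Second, a reader might see a conflict with Section 7, which says "The study analysis will incorporate data collected before" the end of the intervention. There is none. That sentence sits in a monitoring paragraph and does not promise to keep partial forms, so both statements can hold.

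Third, a reader might infer from the percentage scoring in Section 5.2 that the protocol already allows a partial ODI to be scored. It does not say that the denominator shrinks for blank domains. Scoring over the answered domains is a proposal of this review.

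Fourth, it is tempting to add the loss of precision and power of a complete-case ANOVA under progressive visit dropout. That loss comes from dropout and would remain if the removal sentence were deleted, so it does not measure this rule.

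Finally, missing-data methods are often left to an analysis plan that is not shown here. That is fair for the missing method. It does not cover a stated instruction to remove data, since a later plan cannot analyse forms taken out at the data-management stage.

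**Conclusion.** The point holds. As written, the removal rule together with a repeated measures ANOVA can discard observed primary-outcome data and select the analysed set on form completion, and the intention-to-treat fallback does not undo this.

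The size is not known from the documents. If unfinished includes forms with blank domains, and 5% (2% to 10%) of ODI forms are affected independently at five visits, about 19 (23 to 15) of 25 expected completers remain in the primary test. With four visits it is about 20 (23 to 16). With clustering at 5% and five visits it is about 21 to 23. The mechanism does not depend on which visit count is right.

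This should be fixed, but it does not by itself invalidate the trial. It is one loosely worded data-handling sentence whose effect ranges from slight to substantial with its interpretation.

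**What to change.** 1. Delete the removal rule in Section 8.1 and state that all submissions are kept, complete or not.
2. State in advance the minimum number of answered ODI domains needed for a score. Above it, score the form as the sum divided by 5 × the number of domains answered, expressed as a percentage.
3. Replace the complete-case ANOVA with a mixed model for repeated measures that uses all available visits of all randomised participants.
4. Report the amount of missing ODI data by arm and visit.

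The cost is a change of wording and slightly more data handling. There is no added burden on participants. The change should be in force before any form is discarded.
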